#### Measures related to advance directive and ACP documentation

Standard ACP is measured by the completion of advance directives in the VA electronic medical record. We will assess baseline advance directive completion rates and the date the advance directive was signed as well as ACP discussions. At 6 months (date of the last follow-up interview), we reassess the advance directive completion rate and the date it was signed to determine length of time from study enrollment to documentation. An advance directive for the purposes of this study includes the VA or easy-to-read advance directive, a living will, a durable power of attorney for health care document (DPOAHC), a Physicians Orders of Life Sustaining Treatment form, or other documentation of the patient’s wishes for medical care (code status, such as full code or do not resuscitate or do not intubate orders by a physician).

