## Outcomes and Sample Size Calculations

### Primary outcome

The primary outcome is advance directive documentation in the medical record. This outcome was selected based on prior studies that have shown that advance directive interventions can increase documentation. A meta-analysis demonstrated a pooled effect size of 0.50 (95 % CI; 0.17-0.83) suggesting a positive effect associated with advance directive interventions [36]. One RCT of an ACP workbook in older Veterans also demonstrated an increase in living wills documented from 23 % in controls to 48 % in the intervention group (*P* < .001); and ACP notes from 24 % to 47 % (*P* < .001) [37]. Consistent with results from prior studies, our pilot study showed that a literacy appropriate advance directive doubled completion rates from baseline [12]. From SFVAMC administrative data, 11 % of the potential study sample had an advance directive in their medical record. We assume that after being included in the study, the control group may have an advance directive documentation rate of 15 %. If we assume doubling of the percent of ACP discussion notes between groups (what we consider clinically significant), a sample size of 350, or 175 in each arm, will afford us 92 % power with a two-tailed alpha of 0.05 to detect an elevation in rate of advance directive documentation from 15 % in controls to 30 % in the PREPARE group and 80 % power to detect a difference of 15 % in controls versus 27 % in the PREPARE group. After accounting for an estimated 15 % attrition rate, including death at 6 months (based on prior work) [12], our recruitment target is 410 Veterans or 205 in each arm.

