### Data analysis

#### RCT efficacy analysis

Our primary analyses will compare advance directive completion rates and change in engagement in the five ACP behaviors (see Primary outcome section) using behavior change measure scores on a 5-point Likert scale (analyzed as average Likert scores and total scores of 57 to 285) and action measure scores using yes and no responses (scores 0 to 25) from baseline to 1 week, and 3, and 6 months between study arms. We first will use means, medians, and ranges to describe continuous variables, and we will use proportions to describe categorical and dichotomous variables. Baseline comparability of the two groups will then be assessed using t-tests for continuous variables and chi-square tests for proportions. To examine the outcomes between the two study arms longitudinally, we will use mixed effects linear, Poisson, or negative binomial regression for continuous outcome measures and mixed effects logistic regression for dichotomous measures. The mixed effects models will include a random effect for subjects and fixed effects for the primary modeling terms of time, study arm, and an interaction term of study arm and time. We will treat the time variable in three different ways: (i) our first model will encode the time variable as a dummy variable for baseline versus the post-intervention time points; (ii) we will next model time in a continuous linear fashion; (iii) we will lastly consider an arbitrary time course by treating time as a categorical factor variable. We will also adjust for the randomization blocking factors of health literacy (limited versus adequate) and race (white versus non-white) [39] and for any predictor variables that differ between study arms at baseline. We will also include random physician intercepts to account for nesting of patients within physicians. We will consider including random effects for the primary modeling terms of time, study arm, and their interaction. Modeling decisions (for example, which mean structure to use and which random effects to include) will be based on comparing values of the Akaike Information Criterion. Models will be fit using the xt routines in Stata. Mediation analyses will use Stata’s mediation package, which allows estimation of the average causal mediation effect using a potential outcomes framework with either continuous or binary outcomes and allows for sensitivity analyses with respect to violation of the sequential ignorability assumption [40]. Moderating variables will be tested with interaction terms.

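### The subject-random-intercept logistic model set for chart documentation has no finite arm-by-time odds ratio if documentation is cumulative and does not reverse, and a fragile one if it rarely does

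*Protocol article*

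**What the plan says.** Under Primary outcome: "The primary outcome is advance directive documentation in the medical record". The section on measures of advance directive and ACP documentation has the chart read at baseline ("We will assess baseline advance directive completion rates and the date the advance directive was signed") and again at 6 months, with the signing date. The definition there also takes in code status orders, and the Aims section adds clinicians' notes.

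Under RCT efficacy analysis the outcome is named among the primary analyses: "Our primary analyses will compare advance directive completion rates and change in engagement in the five ACP behaviors". The method is "mixed effects logistic regression for dichotomous measures", and the structure is "The mixed effects models will include a random effect for subjects and fixed effects for the primary modeling terms of time, study arm", with an arm-by-time interaction. Baseline is a response row, not a covariate: "our first model will encode the time variable as a dummy variable for baseline versus the post-intervention time points". Time is then also coded as linear and as categorical. The choice of mean structure and random effects "will be based on comparing values of the Akaike Information Criterion". No other estimator is given for the chart outcome.

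On rates, the Primary outcome section reports that "11 % of the potential study sample had an advance directive in their medical record", and then assumes 15% for controls after enrolment and 30% (or 27%) for PREPARE.

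**The concern.** A random-intercept logistic model learns the spread between subjects from how often the same subject changes in each direction. A document in the chart tends to stay there. If no Veteran moves from documented to undocumented, the data look as if each Veteran's outcome were fixed by an infinitely spread intercept. The likelihood keeps rising as the subject SD grows, and every log odds ratio grows in proportion.

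The model's effect measure for the primary outcome would then be whatever value the fitting routine stopped at, and its standard error and Wald p value would mean little. The time codings and the subject effect suit the four-visit survey scores; the chart outcome has been placed under the same rule.

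**Working it through.** **The plan's own figure.** Two-proportion power at 175 per arm, two-sided 0.05: 15% v 30% gives 92.3% (stated 92%), and 15% v 27% gives 79.0% (stated 80%). Both reproduce, as a simple comparison of two proportions and not as the mixed model.

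**Inputs.** From the Primary outcome section: 175 per arm; 11% × 175 ≈ 19 documented at baseline in each arm; 15% × 175 ≈ 26 (control) and 30% × 175 ≈ 52 (PREPARE) at 6 months. Assumptions: the 11% applies to enrolled Veterans, is carried forward, and does not reverse.

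| Pattern (baseline, 6 months) | Control | PREPARE |
|---|---|---|
| no, no | 149 | 123 |
| no, yes | 7 | 33 |
| yes, no | 0 | 0 |
| yes, yes | 19 | 19 |

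**Model.** logit P(y = 1) = b0 + b1·time + b2·arm + b3·arm·time + u, with u normal, mean 0, SD σ. For each fixed σ the likelihood was maximised over b0 to b3 by fine-grid integration.

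| σ | log-likelihood | interaction OR = exp(b3) |
|---|---|---|
| 0 | −300.24 | 2.42 |
| 1 | −279.17 | 2.8 |
| 4 | −238.53 | 9.2 |
| 8 | −231.49 | 55 |
| 16 | −229.63 | 3.0 × 10^3 |
| 32 | −229.31 | 1.2 × 10^7 |

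The best log-likelihood that any model can reach on these counts is the sum of n·log(n/175) over the cells, which is −229.29. It is reached only in the limit, so there is no finite maximum.

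**Why it diverges.** For large σ the model acts as a threshold on u, so b3/σ tends to Φ⁻¹(52/175) − Φ⁻¹(26/175) = −0.533 + 1.043 = 0.51. At σ = 32, exp(0.51 × 32) ≈ 1.2 × 10^7, as in the table.

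**AIC does not help.** Dropping the subject effect costs about 71 log-likelihood units (300.2 − 229.3), so AIC keeps it.

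**Algorithm dependence.** Ordinary Gauss-Hermite fits with 7, 12, 20 and 30 points gave odds ratios of about 3 × 10^95, 2 × 10^19, 2 × 10^19 and 4 × 10^10. These were not run in Stata. They show only that the answer depends on the routine.

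**A few reversals.** Moving 1, 2 or 4 Veterans per arm from yes-yes to yes-no:

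| Reversals per arm | σ at maximum | interaction OR | marginal 6-month OR |
|---|---|---|---|
| 1 | about 7 | about 30 | 2.47 |
| 2 | about 5.5 | about 16 | 2.52 |
| 4 | about 4 | about 9 | 2.63 |

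The marginal odds ratio hardly moves; the subject-specific one falls by more than two thirds on three extra charts per arm. A subject-specific odds ratio is expected to exceed a marginal one, so the gap alone is not an error. The dependence on so few charts is.

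**Test of the interaction.** The likelihood-ratio statistic is 13.5 at σ = 16 (2 × (236.377 − 229.627)) and 14.1 at σ = 32 (2 × (236.358 − 229.309)). It settles.

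**Finite alternatives on the same counts.** Marginal 6-month OR = (52/123)/(26/149) = 2.42; risk difference = 52/175 − 26/175 = 14.9 points; OR among Veterans undocumented at baseline = (33/123)/(7/149) = 5.71.

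**The case against.** The strongest reply is that non-reversal is nowhere stated. The outcome includes code status orders and, in the Aims, clinicians' notes, and the article does not say that these persist. This stands: with even one reversal per arm the estimate is finite. It does not rescue the model, because the value then rests on a handful of charts.

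A reader might infer that the model fails on every reading. It does not. If baseline records presence and 6 months records only newly signed documents, the same planning counts give a maximum at σ = 0 and an odds ratio of about 5.6, though this sets two different quantities side by side over time. If signing dates are used to build values at all four visits (timing assumed), the baseline-versus-post coding is also finite (σ about 10 to 12, OR about 14 to 18). Linear and categorical time still rise up to σ = 32, the largest value tried.

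A reader might infer that the primary test is lost. The likelihood-ratio test settles; the odds ratio, its interval and the Wald p value are what cannot be trusted.

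A reader might also recast the planned effect as 4% v 19% new documentation, with a gain in power. The article does not say that the 15% and 30% contain the 11%, which comes from administrative data on potential participants.

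Last, an article condenses its plan, and a separate analysis plan may handle the chart outcome differently. That would excuse silence. Here the article names this outcome in the primary analyses and assigns the model for dichotomous measures.

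**Conclusion.** The point holds conditionally. On the natural reading (chart presence, cumulative, read twice, no reversals) the stated model has no finite arm-by-time odds ratio: it passes 10^7 at a subject SD of 32 and is still rising, against a marginal odds ratio of 2.42. With 1 to 4 reversals per arm it is finite, about 30 down to 9, and driven by those charts. The conclusion rests on three assumptions: the 6-month value is cumulative, reversals are rare or absent, and the planning rates are roughly right. The article fixes neither of the first two.

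The effect estimate for the primary outcome is at stake, so the plan should be corrected before analysis. The documents do not support saying that the model fails on every reading, that the significance test is arbitrary, or that the outcome must be redefined as new documentation only.

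**What to change.** 1. State whether the 6-month chart value is cumulative presence or documentation newly signed since enrolment.
2. For this outcome, replace the longitudinal mixed model with one 6-month binary outcome per Veteran. Use logistic regression on arm, the literacy and race blocking factors and baseline documentation status, with physician-robust standard errors or a physician intercept, and report a risk difference. A GEE or other marginal model is an acceptable alternative.
3. Say which effect measure is primary. The planning counts give 2.42 marginally and 5.71 among Veterans undocumented at baseline. With strictly no reversals, baseline status predicts the 6-month value perfectly for those already documented. Its own coefficient then diverges while the arm odds ratio stays finite at 5.71 and comes only from the undocumented. The risk difference or the marginal model avoids this.
4. Keep the subject-level mixed models for the survey scores. New documentation from signing dates can be a sensitivity analysis.

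The cost is a change of wording: baseline status and signing dates are already collected, and no new data are needed. The small downside is that the chart outcome has its own model, separate from the survey outcomes. Recruitment of Veterans is complete, so the change should be dated and made before outcomes are compared by arm.

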Functional status	Activities of Daily Living (ADL) and Instrumental Activities of Daily Living (IADL)	15	Morbidity/mortality correlation [51, 52]		X			
Self-rated health status	In general how would you rate your health? (5-pt Likert)	1	Correlation with global health, spearman’s rho = -63, and mortality [53]	X				
Self-rated quality of life	In general, how would you rate your overall quality of life in the past week (5-pt Likert)	1	Test-retest coefficient = 0.81 [54]	X				
Comorbid illness	Determined by ICD-9 codes (chart)	0	Mortality c-stat: [23]		X			
	Charlson comorbidity score [24]		Charlson = 0.704					
	Elixhauser comorbidity score [55]		Elixhauser = 0.793					
Social support	Modified Medical Outcomes Study Social Support (mMOS-SS)	11	Cronbach’s α = 0.88-.93 [56]		X			
Religion/spirituality	Self-reported extent of how spiritual/religious (5-pt Likert) and role play in decision-making.	4	Spirituality associated with quality of life. Religiosity associated with wanting all measures to extend life [57]		X			
Prior ACP experience	Prior ACP experiences (for example, Ever had to make life threatening medical decisions?”) [12]	5			X			
Major life changes	For example, “In the past 6 months, have you or someone close to you been faced with a serious medical problem or diagnosis?”	4						X
	Mediator variables^a^ (also measured as Outcome Variables)							
Baseline knowledge	Knowledge subscales of the ACP Engagement Survey.	6	Cronbach’s α = 0.84 (0.76-0.90), ICC = 0.70 (0.50-0.82) [15]		X			
Baseline self-efficacy	Self-efficacy subscales of the ACP Engagement Survey.	6	Cronbach’s α = 0.83 (0.75-0.89), ICC = 0.60 (0.41-0.76) [15]		X			
Baseline readiness	Readiness subscales of the ACP Engagement Survey.	10	Cronbach’s α = 0.92 (0.88-0.95), ICC = 0.60 (0.53-0.81) [15]		X			
Baseline barriers	Checkbox of 13 common barriers	13	Associated with ACP [25]		X			
Baseline attitudes	Processes of Change for ACP [16]	34	Responsive to an ACP intervention [15]		X			
Desired role in decision-making	Control Preference Scale (CPS) [58]	2	Correlation between preferred and actual role in decision-making [59–61]		X			X
	Primary Outcome Variables							
Full process of ACP	ACP Engagement Survey: Process Measures of knowledge, contemplation, self-efficacy, readiness	116	Process Measures: Cronbach’s α = 0.94 (0.91-0.96), ICC = 0.70 (0.54-0.82) [15]		X	X	X	X
	Action Measures: completion of advance directives, discussions		Action Measures: ICC = 0.87 (0.79-0.92) [15]					

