### Secondary outcomes

The secondary outcomes of this study include a comprehensive range of five specific ACP behaviors: 1) identification of a surrogate, 2) identification of values and goals, 3) choosing the level of leeway or flexibility in decision-making for the surrogate, 4) communicating this information with clinicians and surrogate decision-makers, and 5) documenting one’s wishes. We hypothesize that the scores from these ACP engagement items could be 50 % higher in the PREPARE group compared to the control group. Based on a pilot, the mean engagement scores for older outpatients were 30.7 points out of 57 ± SD of 10. Therefore, we expect a mean score as high as 40 points, a 10-point average difference between PREPARE and controls. However, even an increase of three points may represent a new action in any of the five domains. Using a two-tailed alpha of 0.05, 175 veterans in each randomization group will give us > 99.9 % power to detect a 10-point difference in engagement score, 96 % power to detect a four-point difference, and 80 % power to detect a three-point difference. A sample size of 350 will also allow us to assess each of the five domains of the preparation engagement survey separately as dichotomous variables, “action taken/no action taken”. If we assume a doubling of the percent of Veterans who “took action” within each of the five domains, using a two-tailed alpha of 0.05, we estimate that 175 veterans in each randomization group will give 92 % power to detect a doubling in the percent of Veterans who “took action” from 15 % (controls) to 30 % (PREPARE group) and 88 % power to detect a difference of 15 % versus 27 %. Taking into account an anticipated 15 % drop out as describe above, our anticipated 410 Veterans or 205 in each arm will provide us ample power to assess these outcomes.

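### For the continuous ACP process scores, the planned arm-by-time model estimates a raw change from baseline; adjusting for the baseline score would be more precise at no cost in data

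*Protocol article*

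**What the plan says.** RCT efficacy analysis, under Data analysis, compares change in engagement "from baseline to 1 week, and 3, and 6 months between study arms". The process scores are to be "analyzed as average Likert scores and total scores of 57 to 285". The mixed models contain a subject random effect and "fixed effects for the primary modeling terms of time, study arm, and an interaction term of study arm and time".

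Three codings of time are listed. In order: "our first model will encode the time variable as a dummy variable for baseline versus the post-intervention time points"; then "we will next model time in a continuous linear fashion"; and last an "arbitrary time course by treating time as a categorical factor variable". The first coding shows that the baseline score is part of the modelled outcome.

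Adjustment is named for health literacy, race and any predictor that differs between arms at baseline. No statement adjusts the treatment effect for the baseline score or sets the arms' baseline means equal.

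Two further places supply the inputs. Table 2 gives reliability as "Process Measures: Cronbach’s α = 0.94 (0.91-0.96), ICC = 0.70 (0.54-0.82"), and the section on validity and reliability of the ACP Engagement Survey says this is a 7-day value. The Secondary outcomes section claims "96 % power to detect a four-point difference, and 80 % power to detect a three-point difference".

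**The concern.** The process scores are measured in the same way at baseline, 1 week, 3 months and 6 months. In a randomised trial the true baseline means are equal, so a free study-arm term at baseline estimates a quantity known to be zero. Its sampling error then enters the treatment effect through the interaction.

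What is at stake is precision on outcomes that the authors rate highly. The efficacy section includes the engagement scores among its primary analyses, Table 2 lists the Engagement Survey under primary outcome variables, and Aims and primary hypotheses gives the secondary outcomes equal clinical weight. All 410 Veterans are recruited, so further precision can come only from the analysis.

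The point covers the continuous process scores, and other continuous outcomes measured identically at baseline and follow-up, where a linear mixed model is fitted.

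**Working it through.** **Inputs.** SD 10, a 3-point difference, 175 per arm and two-sided 0.05 come from Secondary outcomes. The 7-day ICC of 0.70 comes from Table 2. The baseline-to-6-month correlation is not given, so ρ = 0.5 is an assumption.

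**The stated power.** For a plain two-sample comparison, SE = 10 × √(2/175) = 1.069.
- 3 points: 3/1.069 = 2.806; Φ(2.806 − 1.960) = 80.1%.
- 4 points: 4/1.069 = 3.742; Φ(3.742 − 1.960) = 96.3%.

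Both stated figures reproduce, but for a comparison that ignores baseline, which is not the planned model.

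**What the planned model estimates.** The stated random-intercept model was fitted to one simulated complete trial (350 patients, ρ = 0.7).
- With categorical time, the 6-month interaction was 3.8123, identical to the raw difference in mean change.
- With baseline-versus-post coding, it was 4.4697, again identical to the raw contrast.
- Adding the baseline score as a main-effect covariate left the 6-month estimate at 3.8123 and its SE at 0.857. The provision for predictors that differ at baseline therefore does not help.
- A common baseline mean reduced the SE from 0.857 to 0.789 (categorical) and from 0.700 to 0.614 (baseline versus post).

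**Variance, in units of SD² per arm, equal variances.**
- Single visit: change 2(1−ρ); adjusted 1−ρ². Ratio 2(1−ρ)/[(1−ρ)(1+ρ)] = 2/(1+ρ).
- Mean of three follow-up visits, compound symmetry: change (4/3)(1−ρ); adjusted (1+2ρ)/3 − ρ².

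| Contrast | ρ | Change | Adjusted | Ratio | Power at 3 points, change vs adjusted |
|---|---|---|---|---|---|
| 6 months | 0.5 | 1.00 | 0.75 | 1.33 | 80% vs 90% |
| 6 months | 0.7 | 0.60 | 0.51 | 1.18 | 95% vs 98% |
| Baseline vs all follow-up | 0.5 | 0.667 | 0.417 | 1.60 | 93% vs 99% |
| Baseline vs all follow-up | 0.7 | 0.40 | 0.31 | 1.29 | 99.3% vs 99.9% |

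For example, for 6 months adjusted at ρ 0.5: SE = 1.069 × √0.75 = 0.926; 3/0.926 = 3.240; Φ(1.280) = 90%.

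Over 4000 simulated trials at ρ 0.7, both approaches averaged about 3.0 for a true effect of 3. The variance ratios were 1.19 (6 months) and 1.28 (mean of follow-ups), against 1.18 and 1.29 by formula.

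**Chance baseline imbalance.** If the arms differ by d at baseline by chance, the expected follow-up difference is effect + ρd. Subtracting d gives effect − (1−ρ)d. The change contrast is thus shifted by −0.5d at ρ 0.5 and −0.3d at ρ 0.7; adjustment removes the shift.

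**The case against.** The strongest reply is that the planned interaction is a valid, unbiased estimate of exactly what the section sets out to compare, namely change from baseline. That stands: the loss is one of precision only.

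The practical loss may also be small. The authors expect a difference of about 10 points, where even at ρ = 0 the change contrast has an SE of 1.069 × √2 = 1.512 and power above 99.9%. That stands for the expected effect; the gain matters for the 3-point fallback and other small effects.

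A reader might infer that the stated 80% power is not reached. The documents do not show this. It would need ρ below 0.5, and would then apply only to the 6-month contrast of the categorical coding, which is listed last. The only documented correlation is 0.70, with a lower limit of 0.54; a lower value at 6 months is possible but assumed. For the first-listed coding, the change variance (4/3)(1−ρ) is at most 1 once ρ reaches 0.25, so 80% is kept from there on.

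A reader might also infer that chance baseline imbalance passes in full into the effect. It does not: the fraction is 1−ρ.

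Finally, the SD of 10 and the 3-point difference belong to a score out of 57, whereas the process total runs from 57 to 285. The power figures cannot be carried over with certainty. The variance ratios do not depend on the SD.

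The choice of model by Akaike's criterion is not an answer: the study-arm term is a stated component, and none of the three time codings removes it.

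**Conclusion.** The point holds as a matter of efficiency, not validity. For the continuous process scores, the stated model yields an unadjusted change contrast. Its single-visit variance is 1.18 times that of a baseline-adjusted contrast at ρ 0.70 and 1.33 times at an assumed ρ of 0.5, so 18% and 33% more Veterans would be needed for equal precision. For baseline versus all follow-up, the ratios are 1.29 and 1.60.

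These figures assume equal variances across visits, near-complete data and, for the averaged contrast, compound symmetry. With missing visits, the equality with raw change is approximate. Under linear time, the interaction is a difference in slopes, still not adjusted for baseline. The section also allows Poisson or negative binomial models, to which these formulas do not apply. Nothing here extends to chart documentation, on which the trial's sample size rests, or to the action items.

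**What to change.** For the continuous outcomes fitted with a linear mixed model and measured identically at baseline and follow-up, drop the study-arm term at baseline so that both arms share one baseline mean. The fixed effects are then time, arm by post-baseline time, literacy and race. Alternatively, model only the 1-week, 3-month and 6-month scores, with the baseline score as covariate. Report the adjusted between-arm difference as the effect.

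This is one change to the model statement. It needs no new data, visits or patients, and the same Stata routines can fit it. The small downside is reliance on equal baseline means by randomisation. If a real arm difference existed at baseline and persisted to follow-up, the adjusted estimate would carry 1−ρ of it and the change contrast none. If instead an artefact shifted only the baseline scores, the adjusted estimate would carry about ρ of it and the change contrast all of it.

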#### Measures related to ACP engagement including behavior change process measures and ACP actions

Full ACP engagement is measured by Veteran self-report at baseline, 1 week, 3 months, and 6 months. Based on Social Cognitive Theory and Behavioral Change Theory [18, 19], we included measures to capture theoretical constructs related to contemplation of behavior, planning or intention to act on the behavior, and the behavior itself. If only the action behavior is measured, such as completion of an advance directive, clinically significant movement along the behavior change pathway will be missed. Thus, it is important to ascertain ACP process measures of behavior change (knowledge, contemplation, self-efficacy, and readiness) for several ACP actions in addition to whether they have completed an ACP behavior (Action Measures). These actions include 1) identifying of a surrogate, 2) identifying values and goals, 3) choosing the level of leeway or flexibility in decision-making for the surrogate, 4) and communicating this information with clinicians and surrogate decision makers, and 5) documenting one’s wishes [22]. As Veterans may have had varying degrees of experience with ACP, we assess baseline engagement in ACP within the past 5 years (standardized based on pilot data). We also ask about engagement in ACP since the randomization date, for example, “Within the past one week, 3 or 6 months”, depending upon the follow-up interval.

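### For the four-wave engagement survey outcomes, AIC is allowed to choose which arm-by-time effect is tested, so the confirmatory contrast is not fixed in advance

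*Protocol article*

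**What the plan says.** The RCT efficacy analysis section of the protocol article specifies mixed effects models with time, study arm and their interaction. It continues: "We will treat the time variable in three different ways". The three ways are:

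- (i) "encode the time variable as a dummy variable for baseline versus the post-intervention time points"
- (ii) "model time in a continuous linear fashion"
- (iii) "consider an arbitrary time course by treating time as a categorical factor variable"

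On modelling decisions it then says "which mean structure to use and which random effects to include) will be based on comparing values of the Akaike Information Criterion". No coding is named as the confirmatory one, and no contrast is named as the effect to be reported.

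The models adjust for the two blocking factors (health literacy and race) and "for any predictor variables that differ between study arms at baseline". The check that precedes this is "Baseline comparability of the two groups will then be assessed using t-tests for continuous variables and chi-square tests for proportions"; no threshold for a difference is given.

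The ACP Engagement Survey is collected at four times. Table 2 places it under Primary Outcome Variables, and the RCT efficacy analysis section includes change in engagement in its primary analyses. The Aims and Secondary outcomes sections treat it as secondary. Chart-based documentation is described in the section on advance directive and ACP documentation measures as assessed at baseline and again at 6 months.

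**The concern.** AIC is a reasonable tool for nuisance features such as which random effects to keep. Here it also governs the mean structure, and the mean structure contains the treatment contrast. The three codings are not three ways of estimating one quantity: they answer different questions about the arms. AIC tends to prefer the larger interaction model in just those data sets where the arms happen to diverge, so a test done after the choice no longer has its nominal level.

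Two things are at stake for the survey outcomes. One is the false-positive rate. The other, which does not depend on any simulation assumption, is that a reader cannot say beforehand whether the reported effect will be an average, a rate per month or a set of visit-specific differences.

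The covariate rule raises a lesser, separate concern. In a randomised trial, baseline differences arise by chance and do not show which variables predict outcome. A rule driven by them leaves the adjusted model open until the data are in.

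**Working it through.** **1. The plan's own figures.** The Secondary outcomes section takes SD 10, 175 per arm and two-sided alpha 0.05. Power = Φ(δ / (SD·√(2/n)) − 1.96), with SD·√(2/n) = 10·√(2/175) = 1.069.

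- δ = 3: 3/1.069 − 1.96 = 0.85, power 80.1% (stated 80%)
- δ = 4: 4/1.069 − 1.96 = 1.78, power 96.3% (stated 96%)
- δ = 10: above 99.9% (as stated)

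These figures reproduce. They describe one fixed comparison of two means at 5%, which is what the AIC rule does not guarantee.

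**2. Three codings, three effects.** Take visits at t = 0, 0.25, 3 and 6 months and assumed true arm differences at each. The post-baseline average is the mean of the three follow-up differences (baseline difference 0). The slope is Σ(t − 2.3125)d / Σ(t − 2.3125)², with denominator 23.67.

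| Arm difference at 1 week, 3, 6 months | (i) average | (ii) slope per month | (iii) at 6 months |
|---|---|---|---|
| 3, 3, 3 (sustained) | 3.0 | 6.94/23.67 = 0.29 | 3.0 |
| 0, 1.5, 3 (rising) | 1.5 | 12.09/23.67 = 0.51 | 3.0 |
| 3, 1.5, 0 (fading) | 1.5 | −5.16/23.67 = −0.22 | 0 |

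The fading benefit is positive, negative or zero according to the coding.

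**3. Type I error after AIC selection.** Simulation with no treatment effect: 175 per arm, four visits, SD 10, random-intercept linear model by maximum likelihood, 20,000 runs per trend. The test comes from the coding with the lowest AIC. The correlation of 0.6 and the trend shapes are assumptions. Monte Carlo standard error is √(0.05·0.95/20,000) = 0.15 percentage points at 5%, and 0.21 at 10%.

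| Common trend in both arms | Rejection after AIC |
|---|---|
| Flat | 10.1% |
| Small step | 8.9% |
| Mixed step and slope (two shapes) | 7.6%, 8.0% |
| Linear | 7.7% |
| Clear step | 7.5% |
| Rise then fall (categorical model forced) | 5.1% |

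Each coding fixed in advance gave 4.5% to 5.3%. The excess is the sum over codings of (share selected × rejection when selected):

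- Flat: 0.474·0.090 + 0.478·0.083 + 0.048·0.386 = 0.101
- Clear step: 0.905·0.049 + 0.095·0.317 = 0.074
- Rise then fall: 0.034·0.057 + 0.966·0.051 = 0.051

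Smaller repeats at the same correlation agree:

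- 2,000 runs per trend: 9.7% flat, 8.5% for a 0.1 SD step, 7.3% for step plus growth, 5.4% where the categorical model was mostly chosen.
- 1,500 runs per trend: 9.4% flat, 7.1% for a 0.5 SD step, 5.7% for a rise of 0.1/0.4/0.6 SD, and 5.1% both for 0.2/0.4/0.5 SD and for −0.6/−0.3/−0.1 SD.

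If the categorical model, when chosen, is called positive whenever any of its three visit differences is significant, the range in the 20,000-run simulation is 7.6% to 12.4%. The contrast therefore has to be named as well as the coding.

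**4. The chart outcome.** With two nominal times, 0 and 6 months, the post indicator, linear time and categorical time are rescalings of one variable. In a check data set (350 subjects, binary outcome) all three gave the same interaction statistic, 2.308.

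**5. The covariate rule alone.** Adjusting only when baseline p < 0.05 (threshold assumed), with a single follow-up measure, gave type I error of 4.6%, 4.1% and 3.7% at covariate-outcome correlations 0.3, 0.5 and 0.7. The rule is slightly conservative. With 20 independent baseline variables (assumed), the chance that at least one differs is 1 − 0.95^20 = 0.64. That is how often the model would change, not a false-positive rate.

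**The case against.** The strongest reply concerns size. The 10% figure needs a flat trend in both arms, which is unlikely: both arms receive an easy-to-read directive that, by the article's own account, doubled completion in earlier work. Under uneven trends AIC mostly selects the categorical model and error is close to 5%. Only Gaussian models were simulated, while the plan also allows count and logistic models. All of this stands, and it is why the size is given as a range. It does not answer the undefined effect.

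It could also be said that all three codings will be fitted and reported. With none named as confirmatory, reading off the smallest of the three p-values gives about 11%, so that reading does not help. A separate analysis plan, not shown, may settle the matter, but the article states the AIC rule positively.

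Four stronger readings are tempting and are not supported:

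- **That the trial's powered test is compromised.** Chart documentation is assessed at two times, where the codings are one test.
- **That the covariate rule inflates type I error.** The calculation shows slight conservatism.
- **That change in action scores means nothing because of the recall windows.** At baseline "we assess baseline engagement in ACP within the past 5 years", and follow-up asks about the time since randomisation. This makes within-arm change and slopes awkward to interpret, but the windows are the same in both arms, so the between-arm contrast keeps its meaning.
- **That the baseline score is ignored.** It enters the mixed model as one of the repeated outcomes.

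**Conclusion.** The point holds for the engagement survey outcomes measured at four times. The stated rule lets the outcome data choose among three different arm-by-time effects. Type I error is then about 5% to 10%, depending on a common time trend nobody knows in advance, against about 5% for a single prespecified coding. This rests on Gaussian random-intercept models, an assumed within-subject correlation of 0.6 and assumed trend shapes. That the size and sign of the effect depend on the coding follows from the definitions and needs none of these assumptions.

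The powered chart-based outcome is not affected by time coding, taking its two assessments at their nominal times. The covariate rule is a separate, smaller weakness. It leaves the adjusted model to chance imbalance and, in logistic models, changes which conditional odds ratio is reported, but it does not raise the false-positive rate.

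**What to change.** For each survey outcome, name one time coding (for example, categorical time) and one arm contrast as confirmatory. Keep the other two codings as sensitivity analyses. Restrict AIC to the choice of random-effect and covariance terms.

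Replace adjustment for variables that differ at baseline with the two blocking factors plus a covariate list named in advance and used whatever imbalance is observed. The baseline tests should no longer feed into the model.

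The cost is wording only. Sample size and the stated power calculations do not change. The one statistical price is that categorical time uses a few more degrees of freedom than a simpler trend would if that trend had been guessed correctly.
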